#### Health outcomes

Self-reported general health will be assessed by the question “How is your health in general? Is it…” (very good/good/fair/bad/very bad). This question is recommended by the WHO as a standard and cost-effective measure in health surveys [14] and is used in national [15] and European longitudinal studies (e.g., the European Health Interview Survey—EHIS). In addition, standardized questionnaires that are widely used in respiratory epidemiological studies in adults will be used (the European Community Respiratory Health Survey—ECRHS [www.ecrhs.org/] and the Epidemiological Study of the Genetics and Environment of Asthma—EGEA [egeanet.vjf.inserm.fr]). To assess weight status, the participants will be asked to self-report their weight and height in order to calculate their body mass index (BMI = weight [kg] divided by height [meters] squared).

#### Physical activity, active mobility, and sedentary behaviors

Context-specific active mobility, general physical activity, and sedentary behaviors will be evaluated by questions from the Sedentary, Transportation, and Activity Questionnaire (STAQ) [16, 17]. Perception of active modes (walking and cycling) and characteristics of the neighborhood related to active mobility will also be part of the questions asked to the participants.

#### Perception and use of neighborhood

The perception and use of urban public spaces (such as streets and sidewalks, parks and public-green spaces, and recreational areas) will be assessed by questions from a Daily Life Environment questionnaire (Questionnaire sur l’environnement de vie quotidien, QEVIC) [18]. Specific questions will be also added to include the perception of the food environment (presence of food outlets/restaurants) and details of where, when, and why food outlets were chosen.

### Subsamples of participants

#### Food supply subsample

Participants in the food supply sample will be provided with a short food supply diary to record the details of their household food supplies over a month and asked to save the corresponding grocery store and supermarket receipts, which will be used to accurately assess household food expenditures for food groups. Based on the share of expenditures by food group, the nutritional quality of the household food supplies will be assessed using the revised Healthy Purchase Index (r-HPI) described elsewhere [19]. Briefly, the r-HPI is an index obtained by summing a purchase diversity subscore and a purchase quality subscore, ranging from a minimum score of minus 8 to a maximum score of 17 points, where a higher score reflects a higher quality of the household’s monthly food purchases.

#### Subsample of the food provisioning practices of individuals

Food provisioning practice will be assessed with semi-structured interviews to improve the understanding of the changes over the period of urban intervention regarding the food provisioning practices of individuals (providing details regarding the choice of food outlets and how they justify their shopping practices). All interviews will be fully recorded and transcribed by a professional transcription company or by a member of the research team.

#### Mobility-based real-time air pollution and noise exposure subsample

Pollutant concentrations and noise levels will be measured for one week along the daily itineraries of participants with mobile sensors and time-activity diaries. Particulate matter concentrations (PM_2.5_ and PM_10_ fractions), the temperature, and the relative humidity will be measured with AirBeam3 sensors (HabitatMap, New York, USA), while the nitrogen dioxide (NO_2_) and ozone (O_3_) concentrations will be determined with Cairsens® (ENVEA group, Poissy, France) data loggers that integrate reliable electrochemical gas sensors. Noise levels will be measured using noise dosimeters developed by BruitParif (France). The following noise indicators will be calculated: LAeq, LCeq, LAFmax, and LCFmax data.

### Environmental characteristics and urban interventions

#### Characteristics of built, social, and retail food environments with GIS

Existing geodatabases provided by French public institutions will be used to characterize the social (e.g., population census-INSEE), built (e.g., land-use-IGN), and retail food environments of the study area. For example, the characteristics of the built environment of interest will include the presence of green and blue spaces, street networks, amenities, and pedestrian and cycling infrastructures. Social deprivation can be characterized at the local level based on census variables (housing composition and unemployment rate). The food and built environment characteristics will be completed by field observations (e.g., pedestrian and cycling networks, outlet locations). In addition, we will examine urban and social changes in the study areas and more specifically the possibility of a gentrification effect (e.g., displacement of traditional low-income residents by more affluent households) using census data and field observations.

#### Decision-making process of urban interventions

Semi-structured interviews will be conducted among key stakeholders to examine the follow-up of the decision-making process related to urban interventions. The process of designing the urban intervention program (e.g., which parties are involved, how, and when) will be analyzed, as well as the content of the urban planning strategy, in particular its relevance with regard to health-related outcomes. For the relevant planners involved in the project, the interviews will focus on the genesis and progression of the urban projects as a part of the assessment of the decision-making process. Existing reports such as urban diagnoses and urban expertise (grey literature) related to the study areas and provided by local practitioners and urban planners will be gathered to obtain a better understanding of the spatial context in terms of populations, economy, and urban history.

### Planned statistical analyses

The distributions and correlations among environmental exposures, health-related behaviors, and self-reported health outcomes will be studied at each time point (T0 and T1). The between-period differences will be quantified. Furthermore, we will analyze both cross-sectional (at T0 and T1) and longitudinal dimensions (from T0 to T1) using cluster analyses (e.g., *K-*means analysis) and model-based methods (e.g., mixture modeling techniques or latent class growth analysis) [20].

The associations between environmental exposures and health-related behaviors will be examined using each indicator individually or using the profiles by multivariate regression and spatially explicit models. For instance, multilevel regression models will be performed to estimate associations between changes in the environment (air quality, noise, built, social, and food) and changes in health-related behaviors (food supply and habitual active mobility). Other approaches will be considered to strengthen the impact attribution of the urban intervention to the observed changes. For instance, interrupted time series regressions will be considered for environmental exposures assessed continuously at evenly spaced intervals over time with one well-defined change point (i.e., urban interventions).

The difference-in-difference approach will be used to compare the changes in the outcomes among the participants exposed to the intervention with the change among those who remain unexposed (i.e., the control group).

Additionally, time sequences of the observations (“life-segment”) will be generated for participants included in subsamples. The dynamic processes interrelating the exposures (air quality, noise, social, built, and food), the places visited, and the health-risk outcomes will be examined by using space-time disaggregation of the data: case-crossover analyses allowing each person to be compared with themselves will thus be conducted. Possible effect measure modification by socioeconomic status will be explored using interaction terms and stratified models. Particularly, the reasons why people do or do not use local food outlets and how low-income participants access and perceive the food environment compared to more advantaged segments of the population will be examined.

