## Methods

### Study design

The study is based on a natural experiment approach with a before/after protocol design to assess changes in environmental exposures, health-risk behaviors, and self-reported health outcomes of a resident adult population before (T0) and after (T1) the implementation of a time series of urban interventions.

The changes observed in adult residents located in the intervention areas (“exposed population”) will be compared to those in adults living in control areas (“unexposed population”). Control areas are located close to areas with urban intervention sites but are not themselves subject to urban intervention. As described in Fig. 1, the data collection will be implemented in two stages in both the intervention and the control areas: a first stage at baseline (T0, 2022), and a second stage (T1, 2025) after the urban interventions.

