## Data collection

### Sampling plan

According to the 2018 census data from the INSEE (the French National Institute for Statistics and Economic Studies), 13,025 adults (≥ 18 years of age) reside in the entire study area (including the control and intervention neighborhoods). We will aim to recruit 600 adult participants at baseline to form the core data survey groups (300 in the intervention area and 300 in the control area). Although there is little precedent for sample size calculations for natural experiment studies (Kestens et al., 2019), potentially due to the multidimensionality of urban interventions, this sample size would be sufficient to assess a change in health-risk behaviors in the context of urban redevelopment. Indeed, assuming a power of 90% and an alpha of 0.05, 380 participants will be required to detect the effect reported by Pazin et al. (2016) for instance, i.e. an increase of 32 (95% CI: 15–51) min/week of walking after development of a new walking and cycling route [13].

In addition, we will aim to define three subsamples of participants to assess:

the nutritional quality of the household food supply through a food supply diary for a subsample among 400 participants (200 in the intervention area and 200 in the control area);the food provisioning practices of individuals through a semi-structured interview for a subsample of 30 participants (15 in the intervention area and 15 in the control area);the mobility-based real-time air pollution and noise exposures through sensor measurements for a subsample of 30 participants (15 in the intervention area and 15 in the control area).

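### Latent class growth analysis is named for participant outcomes measured at only two waves, where it shows no trajectory shape and can turn within-person correlation into spurious classes

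*Protocol article*

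**What the plan says.** The Study design section plans two rounds of data collection for exposed and control residents alike, namely "a first stage at baseline (T0, 2022), and a second stage (T1, 2025) after the urban interventions". No third participant wave is described anywhere in the article.

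The Planned statistical analyses section says "we will analyze both cross-sectional (at T0 and T1) and longitudinal dimensions (from T0 to T1) using cluster analyses" (K-means is the example given). Among the further options it lists "model-based methods (e.g., mixture modeling techniques or latent class growth analysis". The next paragraph says that associations between exposures and behaviours will be examined either one indicator at a time or through the profiles, using regression and spatial models. Classes from the first step may therefore become variables in the second.

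The same section assigns other tasks to other methods. Interrupted time series is considered for exposures recorded continuously at even intervals. The subsample sequences go to case-crossover analysis. On the intervention itself the article states: "The difference-in-difference approach will be used to compare the changes in the outcomes among the participants exposed to the intervention"; the comparator is the control group's change.

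**The concern.** Latent class growth analysis groups people by the course of an outcome over time. With one value before and one after, the only course available is the line joining two points. The classes then say no more than a grouping on baseline level and change, yet they would be reported as trajectories.

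The model also has no random effects within class, so all dependence between T0 and T1 must come from differences between classes. The same adult asked twice about walking or general health will usually give correlated answers. The model can represent that correlation only by splitting the sample, even when no distinct groups exist. If such classes are then regressed on environmental change, groups that appear to improve or decline could be given an environmental explanation although they are a by-product of the model.

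**Working it through.** **Inputs.** From the article: two waves (Study design); 600 adults at baseline, 300 per area (Sampling plan). Assumed, because the article gives no value: T0–T1 correlation 0.3 to 0.7, and 420 adults with both waves (420/600 = 70%; the article states no attrition rate). The article has no figure of its own on this point. Its sample-size figure of 380 for walking does not bear on it.

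**1. Trajectory shape.** A linear class trajectory uses 2 mean parameters. With T waves there are T means per class, leaving T − 2 degrees of freedom: 0 at T = 2, 1 at T = 3, 2 at T = 4. At two waves the line always fits exactly, so its form cannot be tested and no curvature can be fitted.

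**2. What can be estimated.**
- A growth mixture with random intercept and slope needs at least 4 covariance parameters (two variances, one covariance, one residual variance). Two waves supply 3 moments (two variances, one covariance), so it is not identified without constraints.
- Latent class growth analysis proper has no within-class random effects and can be fitted. Its classes are separated by the assumed within-class normal shape. With two classes there are 1 + 4 + 2 = 7 parameters (class share, means, residual variances) against 5 first- and second-order moments.
- In 25 simulated data sets of N = 600 with two true classes (change 0 and 3.0 SD), BIC chose two classes in 96%, and the mean estimated changes were 0.03 and 2.94.

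**3. Why correlation creates classes.** Under within-class independence, Cov(T0, T1) = Σ πk (μk0 − μ0)(μk1 − μ1). With one class this is zero, so any real correlation counts against one class. For normal data the log-likelihood-ratio statistic available from modelling a correlation ρ is −n ln(1 − ρ²). At n = 420 and ρ = 0.5 that is −420 × ln(0.75) = 120.8. One extra class costs 3 parameters, a BIC penalty of 3 × ln(420) = 18.1. At ρ = 0.3 the figures are 39.6 and 18.1. A mixture need recover only part of the available gain to be preferred.

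**4. Simulation with one homogeneous population and within-class independence; BIC over 1 to 4 classes.**

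| Setting | 1 class | 2 | 3 | 4 |
|---|---|---|---|---|
| n = 420, ρ = 0.5, normal, 100 data sets | 0 | 14 | 82 | 4 |
| n = 420, ρ = 0.5, log-normal, 100 data sets | 0 | 9 | 32 | 59 |
| N = 600, ρ = 0, normal, 25 data sets | 100% | 0% | 0% | 0% |
| N = 600, ρ = 0.3, normal, 25 data sets | 0% | 92% | 8% | 0% |
| N = 600, ρ = 0.5, normal, 25 data sets | 0% | 4% | 76% | 20% |
| N = 600, ρ = 0.7, normal, 25 data sets | 0% | 0% | 0% | 100% |

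**5. Are two waves the cause?** Same population, n = 420, ρ = 0.5, normal, 40 data sets per row.

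| Model | 1 class | 2 | 3 | 4 |
|---|---|---|---|---|
| 2 waves, independence | 0 | 4 | 36 | 0 |
| 3 waves, independence | 0 | 0 | 28 | 12 |
| 4 waves, independence | 0 | 0 | 3 | 37 |
| 6 waves, independence | 0 | 0 | 0 | 40 |
| 2 waves, within-class covariance allowed | 40 | 0 | 0 | 0 |

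More waves make the over-extraction worse, and allowing the covariance removes it. With log-normal data the covariance model still over-extracts (0/2/14/24 of 40), so skewness is a separate source.

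**6. What the spurious classes look like.** With normal data they differ mainly in level: T1 − T0 change differs by about 0.3 SD between the extreme classes. With log-normal data (log-SD 0.6) the extreme classes differ in change by about 2.3 to 5.7 SD on average over ρ = 0.3 to 0.7. False improvers and decliners are therefore mainly a risk for skewed outcomes, which walking minutes may well be.

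**The case against.** The strongest reply is that the article commits to little. Latent class growth analysis is one example after an e.g., joined by an or to mixture modelling, next to K-means. A condensed article may leave the choice of model to a full analysis plan, and mixture modelling already covers suitable two-wave methods. Profiles are an alternative to single indicators in the regressions. Exposures recorded continuously are not limited to two points, so growth methods are not excluded for them. All of this stands, and it lowers the weight of the point. It does not remove the mismatch: the method is named for the T0-to-T1 dimension, and participants have only those two waves.

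Three stronger readings are tempting, and the documents do not support them:
- **That the model cannot be estimated.** The linear two-wave version is just-identified in its class means and recovered well-separated classes. For five-level self-rated health, an unrestricted two-class model with two items is not identified (17 parameters, rank 15). The usual ordinal version, with thresholds held equal across waves and classes, is locally identified: 8 parameters with rank 8 for two classes, and 11 with rank 11, weakly, for three.
- **That the classes would necessarily be artefacts, and because there are only two waves.** At zero correlation none arose, and at correlation 0.5 the problem grew with more waves. The independence assumption is responsible.
- **That the estimate of the intervention effect is compromised.** It rests on difference-in-differences, which needs only two waves and does not use the classes.

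**Conclusion.** The point holds as a mismatch between a named method and the stated design, at low severity. For participant outcomes at T0 and T1, latent class growth analysis reduces to a latent profile of two values. It cannot show the shape of a trajectory, and its classes may reflect within-person correlation or skewness. Under the assumed correlations of 0.3 to 0.7 the false classes were chosen in nearly every simulated data set. The sample size of 420, the correlations and the distributions are assumptions and not figures from the article. The zero degrees of freedom for shape do not depend on them. The consequence is confined to the profile analyses and to any regression that uses those profiles.

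**What to change.** In Planned statistical analyses, replace latent class growth analysis, for participant outcomes measured at T0 and T1, with a two-wave method. Two are suitable: latent transition analysis on profiles built from several indicators at each wave, or a mixture model that allows T0–T1 covariance within class. Transform skewed outcomes first, because the covariance term alone does not prevent over-extraction. State that classification uncertainty will be carried into any regression on profiles, rather than treating the most likely class as known. Keep growth methods only for exposures measured at three or more time points.

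The cost is a short change of wording and slightly more analysis work. No new data are needed, and the planned difference-in-differences analysis stays as it is.

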#### Intervention and control neighborhoods

The UrbASanté study will examine potential changes in environmental exposures, health-related behaviors, and self-reported health due to urban interventions in an urban area called Porte de la Chapelle in the northern part of the city of Paris (France). This area includes four contiguous neighborhoods located in the northern part of the 18th arrondissement of Paris (Fig. 2).

This area exhibits specific characteristics compared to the broader Parisian conurbation: a large part of its population is socioeconomically deprived and it is exposed to high levels of pollutants [11]. This area is also defined as a place of interest in the context of the Olympic and Paralympic games scheduled to take place in Paris in 2024. Urban interventions will occur with different stages of transformation from 2024 (the Paris Olympic and Paralympic games) to 2030 (legacy of the Paris Olympic and Paralympic games) depending on each neighborhood.

Two neighborhoods will be referred to as “intervention” neighborhoods, with measures taken before and after a series of urban changes that will start in 2023 (Fig. 2).

The main urban changes in the Gare des Mines-Fillettes neighborhood (which includes the two urban sections of Charles Hermite and Valentin Abeille) will comprise the creation or renewal of urban green areas, pedestrian/cycle pathways and urban corridors, housing, redesigning of public spaces, and more specifically the construction of an Olympic sports facility.The urban changes in Porte de la Chapelle Avenue will mainly comprise the development of a new public transport network (bus) as well as the inclusion of cycle and pedestrian pathways and the widening of sidewalks.

Two neighborhoods will be referred to as “control” neighborhoods, with measurements at the same time periods as for the “intervention” neighborhoods.

Chapelle-international is a new neighborhood built on the site of a former railway wasteland. At the end of 2019, more than 1,500 residents had already moved into this neighborhood.The Chapelle-Evangile neighborhood will not undergo specific urban interventions, except in the northern part, where the renovation and expansion of a green area are currently being finalized.

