### Study design

A particular methodological challenge for our study is the recruitment of participants in a context of (i) low socioeconomic neighborhoods with deprived populations who are generally a hard-to-reach segment of the overall population for research purposes and (ii) a hot topic (urban changes and health) in “hot places” that receive a great deal of political and urban planning attention in the context of ongoing large urban regeneration programs, especially with the perspective of the Olympic and Paralympic Games taking place in Paris in 2024.

An additional methodological challenge is the ability to identify intervention and control neighborhoods. Ideally, this involves finding similar intervention and control neighborhoods, with the only difference being that one or several of the neighborhoods will undergo an urban change. In practice, none of the neighborhoods are equally matched in terms of all of the characteristics of interest. In our study, the main objective criterion to identify equally matched neighborhoods is the socioeconomic level, which will be used to define disadvantaged vs. more advantaged areas. This design is appropriate for our study because the intervention and control sites are in the same residential area, with urban intervention taking place in specific neighborhoods. While major transport infrastructures or those related to the Olympic Games will benefit all neighborhoods and more broadly all of Paris and its surrounding areas, specific urban interventions (i.e., housing, street, site) are restricted to specific neighborhoods only.

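### Exposure varies only across four neighborhoods, two against two, so a participant-level difference-in-difference cannot separate local drift from intervention effect, and the stated power makes no allowance for area

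*Protocol article*

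**What the plan says.** Under Intervention and control neighborhoods, the Protocol article describes the study area: "This area includes four contiguous neighborhoods located in the northern part of the 18th arrondissement of Paris". It then divides them: "Two neighborhoods will be referred to as “intervention” neighborhoods" and "Two neighborhoods will be referred to as “control” neighborhoods". The Study design part of the Discussion places the exposure at that level: "specific urban interventions (i.e., housing, street, site) are restricted to specific neighborhoods only".

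The impact contrast, in Planned statistical analyses, is worded for individuals: "The difference-in-difference approach will be used to compare the changes in the outcomes among the participants exposed to the intervention", set against the change in those who stay unexposed. Multilevel models appear in the same section for a different question: "multilevel regression models will be performed to estimate associations between changes in the environment" and changes in behavior. Spatially explicit models are also named there, again for associations between exposures and behaviors.

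The Sampling plan counts individuals as well. The recruitment target is 600, "300 in the intervention area and 300 in the control area", and the justification reads "assuming a power of 90% and an alpha of 0.05, 380 participants will be required to detect the effect", the effect being 32 min/week of walking. The article judges this sufficient. It gives no SD, ICC or design effect, and the number of areas does not enter the justification.

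The Limitations section covers the timetable of the works and self-report, but not the small number of areas.

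**The concern.** Residents of one neighborhood share whatever happens there between T0 and T1: shops opening or closing, construction nuisance, transport, safety, turnover of residents. With two areas per side and two time points, a shift common to one neighborhood enters the difference-in-difference exactly as an intervention effect would. Recruiting more residents does not reduce it.

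The article itself gives reasons to expect such shifts. One control neighborhood is newly built and recently populated. The other has a green area being renovated and expanded in its northern part. The Discussion concedes that no neighborhoods are matched on every characteristic, and gentrification is to be examined. The two intervention neighborhoods also receive different packages: green space, housing and an Olympic sports facility in one; a bus network, cycle and pedestrian paths and wider sidewalks in the other. A single pooled contrast would hide which package is being tested.

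At stake is whether a participant-level interval can carry the guidance for urban planning and public health policy that the abstract promises.

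**Working it through.** **Inputs from the article:** four neighborhoods, 2 vs 2; 600 participants at baseline, 300 per side; 380 required; alpha 0.05; power 90%; effect 32 min/week.

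**Assumptions, not in the article:** two-sided alpha; two equal groups; an even split within each side (600/4 = 150 per neighborhood, or 380/4 = 95); an ICC of change from 0 to 0.02.

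**Step 1: the plan's own figure.** Without an SD, 380 cannot be reproduced independently, so I solve for the SD of change that would give it. From n per arm = 2·SD²·(1.960 + 1.282)²/32² with n = 190:

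SD = 32·√(190/2)/3.242 = 96.2 min/week, a standardized effect of 32/96.2 = 0.33.

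So 380 fits an ordinary two-sample calculation with design effect 1. With the same SD, 300 per side gives nominal power of 98%.

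**Step 2: type I error of an independent-errors test.** The design effect is DE = 1 + (m − 1)·ICC, and the true type I error is 2·[1 − Φ(1.96/√DE)]. At m = 150 and ICC 0.01, DE = 1 + 149·0.01 = 2.49, and 2·[1 − Φ(1.96/1.578)] = 0.214.

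**Step 3: area-level inference.** Four areas in two groups leave 4 − 2 = 2 df, with critical value 4.303 instead of 1.960. The participant-level half-width at 600 is 1.96·96.2·√(2/300) = 15.4 min/week. The area-level half-width is 4.303·96.2·√(2/300)·√DE. Power on 2 df uses the noncentral t.

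| ICC (assumed) | DE, m = 150 | Type I, N = 600 | Type I, N = 380 | Half-width on 2 df, N = 600 | Power on 2 df, N = 600 | Power on 2 df, N = 380 |
|---|---|---|---|---|---|---|
| 0 | 1.00 | 5.0% | 5.0% | 33.8 | 58% | 43% |
| 0.001 | 1.15 | 6.7% | 6.1% | 36.2 | 53% | 41% |
| 0.005 | 1.75 | 13.8% | 10.6% | 44.7 | 40% | 33% |
| 0.01 | 2.49 | 21.4% | 15.9% | 53.3 | 31% | 27% |
| 0.02 | 3.98 | 32.6% | 24.8% | 67.4 | 23% | 21% |

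The type I columns need only m and the ICC. The half-width and power columns also rest on the back-solved SD. At ICC 0.01, power on 2 df stays below about 45% however many residents are recruited, because the between-area term does not shrink with m.

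**Step 4: permutation.** There are C(4,2) = 6 ways to choose two areas of four, so the smallest two-sided exact p-value is 2/6 = 0.33.

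**Sensitivity.** One intervention neighborhood contains two urban sections. Counting them separately gives 3 vs 2 areas and 3 df, which does not alter the conclusion.

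**The case against.** The strongest reply is that the article states no variance estimator. Comparing changes among participants says whose outcomes are compared, not that errors are independent, and a condensed article may leave the specification to a fuller plan. That is fair: a reader might infer that the authors have committed to independent errors, and the text does not say so. But no estimator creates more than four exposure units. A neighborhood random effect or cluster-robust variance from four areas is not reliable, and the multilevel models that are named are tied to another question. The sufficiency claim in the Sampling plan is already made at participant level.

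Second, the ICC of change may be small. The areas adjoin, and change scores remove stable differences between them. At ICC 0 the participant-level test is valid, and at 0.001 the inflation is slight. This stands. A reader might infer that the intervals are shown to be far too narrow; the documents do not establish that, because they give no ICC.

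Third, a reader might infer that no neighborhood-level test could reach 0.05. That is true of the exact permutation test only. A t-test on 2 df can reach it, with the power shown above.

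Fourth, inference about these four areas is a legitimate target, and the article does not rule out neighborhood-specific results. Both points stand, but the article neither states that restriction nor lists the few areas among its limitations.

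**Conclusion.** The structural point holds. Exposure differs between two and two neighborhoods, while the difference-in-difference and the 380/90% statement are framed on participants with no allowance for area. Neighborhood-specific drift from 2022 to 2025 is not separable from the intervention effect, whatever standard error is used.

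The size is conditional. For a nominal 5% independent-errors test with 150 per neighborhood, the true type I error runs from 5% to 33% as the ICC of change goes from 0 to 0.02, and becomes material from about 0.005 upward. With fewer residents at T1 the inflation is smaller: 16% instead of 21% at ICC 0.01 if 380 remain. The ICC range and the even split are my assumptions, and the power and half-width figures also depend on a back-solved SD of 96.2 min/week.

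A reader might also infer that clustering standard errors by building or census block would cure the problem. It would not: those units lie below the neighborhood, so a shock shared by the whole neighborhood stays in the contrast.

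**What to change.** In Planned statistical analyses:

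- Report the four neighborhood-specific T0–T1 changes, and each intervention neighborhood's own contrast with the controls, beside any pooled estimate, because the two packages differ.
- State that inference on the intervention–control contrast is conditional on these four neighborhoods and that area shocks cannot be separated from the intervention.
- Where home location is available, add proximity to completed works, from the GIS data already planned, as a supporting analysis. The article does not say that home addresses are collected, and proximity will remain closely tied to neighborhood, so this should not replace the first two items.
- Building- or block-level clustering may be used, but must not be presented as removing neighborhood-level shocks.

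In the Sampling plan, state that 380 for 90% power assumes no between-neighborhood variation in change, give the SD used, and show power over a range of ICCs.

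The cost is mainly analysis and wording, best settled before T1 results are seen. The downside is wider intervals and a less favourable stated power.
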